### Study intervention

2.5

The RADIA trial includes a 14-day screening period used to determine participant eligibility. Prior to this screening period (specifically, within 90 days before randomization), individuals must have received first-line treatments such as high-dose intravenous corticosteroids, intravenous immunoglobulin (IVIg), and/or plasmapheresis. Importantly, participants who have received at least 2 doses of FcRn antagonist efgartigimod are still eligible for enrollment. The treatment period of the RADIA trial begins at the time of randomization. Participants will be randomized to receive either BCDT followed by daratumumab, BCDT, or repeated IVIG/PE.

The strategy of BCDT refers to multiple sclerosis. Anti-CD20 ofatumumab is administered subcutaneously at a dose of 20 mg at weeks 0, 1, and 2 (loading doses), followed by 20 mg every 4 weeks from week 4 to week 24 (maintenance doses: weeks 4, 8, 12, 16, 20, 24).

Daratumumab will be administered intravenously on the day after each ofatumumab administration. The daratumumab dosing schedule is: 8 mg/kg at weeks 0, 1, 2, and 4 (loading dose), followed by 4 mg/kg at weeks 8, 12, 16, 20, and 24 (maintenance dose). Pre-medication (corticosteroids, antihistamines, and antipyretics) is required before each daratumumab infusion to minimize infusion-related reactions.

In this study, each administration of daratumumab is defined as one treatment cycle. A total of 9 administrations are planned at weeks 0, 1, 2, 4, 8, 12, 16, 20, and 24, resulting in a total treatment duration of approximately 24 weeks. The effects of this daratumumab regimen will be evaluated throughout the study period. Laboratory tests will be required before each dose of the study drug to determine if any dose adjustments are necessary. During the study, patients should receive comprehensive supportive care as appropriate, aligned with their institutional guidelines. Necessary concomitant medications or treatments to ensure adequate supportive care, such as anti-epileptic drugs, may be prescribed. The following concomitant medications are strictly prohibited during the study: natalizumab, cyclosporine, mitoxantrone, mycophenolate mofetil, and azathioprine.

For adolescent patients aged 12–18 years, the doses of study drugs are consistent with the dosing regimen for adult patients. The safety and efficacy of ofatumumab in this age group have been established, and the dose is identical to that used in adults (22–25).

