Concomitant medications and dosage	**×**	**×**	**×**	**×**	**×**	**×**	**×**	**×**	**×**	**×**	**×**	**×**	**×**	**×**	**×**	**×**	**×**	**×**	**×**	**×**
Statistical analysis												**×**								**×**

Assessments will be conducted by the study team before randomization; after each study drug cycle at weeks 6, 16, and 24; and during follow-up at week 48. Neurocognitive performance will be measured via the Mini-Mental State Examination (MMSE), the Montreal Cognitive Assessment (MoCA), and the Neuropsychiatric Inventory (NPI) will be anti-neuronal antibody titres and other relevant markers will be analysed in serum and cerebrospinal fluid at baseline and week 16 following the initiation of the study drug treatment. For further details, please refer to the enrollment, intervention, and assessment schedule outlined in Table 1. Routine blood parameters will be assessed before each administration of the study drug, on day28 after each cycle, and at week 16 to monitor for potential drug-induced side effects, including thrombocytopenia, leukopenia, and elevated liver enzymes. Additionally, the length of stay in the ICU after the commencement of the study drug will be recorded at the conclusion of the study. Adverse events, including serious adverse events (SAEs), will be monitored continuously from the first administration of the study drug until 1 year after treatment initiation or until withdrawal from the clinical trial, whichever occurs first. Safety monitoring will therefore cover both the treatment period (up to Week 24) and the subsequent follow-up period (Weeks 24–48).

To reduce assessment bias, all outcome evaluations, including mRS, CASE, and neurocognitive assessments are performed by trained neurologists who are not involved in treatment allocation. All assessment sessions are video recorded and subsequently reviewed by at least one additional independent neurologist blinded to treatment group assignment. In cases of discrepancy, a third independent neurologist adjudicates the final score, ensuring that final outcome scores are based on a blinded adjudication process.

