### Discontinuation of the study protocol

2.8

The study maybe terminated for individual patients if the patient or their legal representative withdraws consent. Additionally, the investigator may terminate a patient’s participation at any time during the study if the patient meets any of the following termination criteria:*Hepatic function*: AST/ALT levels are ≥ 3 times the upper limit of normal (ULN), bilirubin levels are ≥ 2 times the ULN (with direct bilirubin accounting for at least 35% of the total), or the INR is > 1.5 (note that INR values do not apply to patients taking anticoagulants).*Cardiac safety*: Investigational medicinal products (IMPs) must be discontinued in patients who meet one of the following ECG criteria on the basis of the average of three readings: QTcF >500 ms, uncorrected QT > 600 ms, or QTcF change from baseline > 60 ms.*Infection*: The patient developed suspected new latent tuberculosis infection (LTBI), active tuberculosis (TB), or nontuberculous mycobacterial (NTM) infection during the study (including but not limited to confirmed conversion by interferon gamma release assay [IGRA] or other diagnostic methods).*Adverse reactions*: Significant unexpected adverse reactions, unexpected reactions of high severity, or other important safety results as determined by the Independent Data Monitoring Committee (IDMC).The trial site may also terminate or suspend the trial early if serious violations of good clinical practice (GCPs), the study protocol, or contractual agreements are identified, or if the site is unable to ensure sufficient enrollment of subjects.

The DSMB will regularly review the progress of the study and conduct interim assessments of safety data. They will provide recommendations to the sponsor regarding whether the nature, frequency, and severity of adverse reactions related to the study treatment warrant early termination or modification of the study to maximize patient benefit. If necessary, the sponsor may decide to terminate the trial.

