### Withdrawal and replacement of individual subjects

2.9

Patients can leave the study at any time for any reason if they wish to do so without any consequences. The attending physician can decide to withdraw a subject from the study for medical reasons. After withdrawal, these patients will receive the standard ICU care.

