The secondary objectives of the study were to analyse the effects of daratumumab on disease severity at various time points throughout the study, as well as its impact on clinical assessment scales (e.g., Clinical Assessment Scale for Autoimmune Encephalitis (CASE) scores, MoCA, MMSE, NPI and laboratory parameters (e.g., blood immunoglobulin, lymphocyte subsets, memory B cells, and plasma cell subsets). Specifically, the secondary endpoints will evaluate the effects of daratumumab on the following:mRS score at 6, 16, 24, and 48 weeks following the first dose of the drug.CASE scores at 6, 16, 24, and 48 weeks following the first dose of the drug.Duration of ICU if patients are staying in ICU at treatment initiation.Cognitive function assessments (MoCA, MMSE, and NPI) will be performed at baseline and at each scheduled study visit, including infusion visits, with the primary analysis conducted at Week 16.Absolute and relative changes in serum autoantibody are measured at baseline and 16 weeks after the first dose of the study drug. To ensure methodological consistency across centers, all antibody testing will be conducted by a third-party central laboratory (KingMed Diagnostics, Guangzhou, China) using standardized commercial cell-based assays (CBA). Antibody positivity and titer interpretation will be determined according to the diagnostic cut-off values and procedures recommended by the assay manufacturers and established clinical protocols for autoimmune encephalitis. Specifically, serum and CSF antibody titers are determined by serial twofold dilutions. Positivity is defined as a serum titer ≥ 1:10 or a CSF titer ≥ 1:1, with a clear cell-surface fluorescence intensity of ≥ 2 + (on a 0–4 + scale) compared to the negative control, in accordance with the manufacturer’s instructions. Borderline results (e.g., titer = 1:10 with 1 + intensity) will be retested in duplicate; persistently borderline results will be reported as indeterminate.Immune status, including lymphocyte subsets, memory B cells, and plasma cell subsets.Safety parameters, including serious adverse events, were monitored within 16 weeks after the first dose of the study drug.

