#### Methods for additional analyses

2.12.3

If the degree of censoring is high, a restricted mean survival time analysis will be performed as a sensitivity analysis to support the main estimator. For missing data in the primary endpoint, multiple imputation under the missing-at-random assumption will be applied, and sensitivity analyses will be conducted under alternative missing-data assumptions to assess the robustness of the primary outcome. In addition, sensitivity analyses will be performed under different response rate assumptions to evaluate the stability of the results.

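### The safety endpoint closes at week 16 although dosing runs to week 24, and toxicity can end a patient's follow-up rather than only the study drug

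*Protocol article*

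**What the plan says.** **Safety window.** The last item in the list of secondary endpoints (section 2.10) reads: "Safety parameters, including serious adverse events, were monitored within 16 weeks after the first dose of the study drug". The same list takes mRS and CASE to weeks 24 and 48. Section 2.5 sets the daratumumab schedule: "A total of 9 administrations are planned at weeks 0, 1, 2, 4, 8, 12, 16, 20, and 24". Ofatumumab also runs to week 24. Section 2.6 then says: "Safety monitoring will therefore cover both the treatment period (up to Week 24) and the subsequent follow-up period", meaning weeks 24 to 48.

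**Leaving the trial.** Section 2.8 lets the investigator end a patient's "participation at any time during the study if the patient meets any of the following termination criteria". The list covers hepatic, cardiac, infection and adverse-reaction criteria. Only the cardiac item is worded as a drug stop: "Investigational medicinal products (IMPs) must be discontinued in patients who meet one of the following ECG criteria". Section 2.9 adds: "The attending physician can decide to withdraw a subject from the study for medical reasons", after which standard ICU care follows.

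**What happens to the data.** Under section 2.6, adverse events are collected "until 1 year after treatment initiation or until withdrawal from the clinical trial, whichever occurs first". Section 2.12.3 says: "For missing data in the primary endpoint, multiple imputation under the missing-at-random assumption will be applied", with sensitivity analyses under other assumptions. Section 2.12.4 carries the last observation forward after withdrawal in sensitivity analyses, and censors time-to-event data at withdrawal as non-informative.

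**The concern.** There are two separate points.

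First, the trial asks whether adding plasma-cell depletion to B-cell depletion is worth its harms. As listed, benefit on mRS and CASE is read to week 48 but harm only to week 16. The last two doses, the aftermath of the week-16 dose and the whole follow-up phase are outside the stated safety comparison between arms.

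Second, a toxicity criterion such as raised transaminases or suspected new latent tuberculosis is a reason to stop a drug. It does not prevent anyone from scoring the mRS at week 16. The text nevertheless allows it to end participation, and with it adverse-event collection. The decision is the investigator's, the trial is open-label, and one arm receives an extra antibody, so exits may differ by arm for reasons tied to treatment. That is where a missing-at-random imputation is least secure. The planned sensitivity analyses can show how fragile the result is, but they cannot restore outcomes that could have been observed.

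**Working it through.** **1. The safety window against exposure and follow-up** (sections 2.5, 2.6, 2.10 and Table 1)

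- Daratumumab doses after week 16: weeks 20 and 24, so 2 of 9 (22%). In dose terms, 2 × 4 = 8 mg/kg of a planned 4 × 8 + 5 × 4 = 52 mg/kg (15%). The week-16 dose falls on the boundary, with no follow-up inside the window.
- Treatment weeks outside: (24 − 16)/24 = 8/24 = 33%.
- Study weeks outside: (48 − 16)/48 = 32/48 = 67%.
- Post-baseline blood-test visits in Table 1: weeks 1, 2, 4, 8, 12, 16, 20, 24, 36 and 48. Four of ten (20, 24, 36, 48) are outside.

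**2. The plan's own design figures** (section 2.11)

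Inputs: response 0.90 against 0.70, two-sided α 0.05, power 80%. With the pooled-variance formula,

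n = [1.96·√(2 × 0.80 × 0.20) + 0.84·√(0.90 × 0.10 + 0.70 × 0.30)]² / 0.20² ≈ 62 per group,

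close to the stated 64. The design figures are therefore usable as working rates. The active arms are set at 80 each, with 10% dropout.

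**3. Power is not the issue.** If patients without a week-16 value were simply dropped equally from both arms, power at 0.90 against 0.70 would be 89% at 80 per arm, 88% at 76, 86% at 72 and 84% at 68.

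**4. Bias in the primary difference, as an illustration.** The protocol gives no toxicity-termination rate and no response rate in such patients, so both are assumed. Let pD and pO be the fractions lost in the daratumumab and ofatumumab-alone arms, and rD and rO the true response rates of the lost patients. If each lost patient is imputed at the arm's rate, 0.90 or 0.70, then

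error = pD·(0.90 − rD) − pO·(0.70 − rO).

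With one common response rate r among lost patients in both arms, the error in percentage points is:

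| Lost (daratumumab / ofatumumab alone) | r = 70% | r = 50% | r = 30% |
|---|---|---|---|
| 5% / 5% | +1.0 | +1.0 | +1.0 |
| 10% / 10% | +2.0 | +2.0 | +2.0 |
| 10% / 3% | +2.0 | +3.4 | +4.8 |
| 3% / 10% | +0.6 | −0.8 | −2.2 |

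For example, 10%/3% at r = 30%: 0.10 × 0.60 − 0.03 × 0.40 = 0.060 − 0.012 = 0.048. If lost patients respond like the rest of their arm, the error is 0 in every row.

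**5. Outer limit without any imputation assumption.** Suppose all of the 10% dropout (8 of 80 per arm) lacked a week-16 mRS.

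- Lowest difference: 0.9 × 0.90 − (0.9 × 0.70 + 0.10) = 0.81 − 0.73 = 0.08.
- Highest difference: (0.9 × 0.90 + 0.10) − 0.9 × 0.70 = 0.91 − 0.63 = 0.28.

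A 20-point difference would thus be bounded only between 8 and 28 points.

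**The case against.** **On the safety window.** Harms after week 16 are not ignored. Section 2.6 follows them for a year and has the DSMB review safety every 8 weeks in weeks 24 to 48, with reporting under the CONSORT harms guidance. Table 1 marks a statistical analysis at week 48 as well as week 16, and a week-16 cut matches the primary time point. On this reading the fault is one inconsistent sentence. This stands in part: for patients who remain in the trial no data are lost, and the 67% describes the endpoint's window rather than missing records. Monitoring and reporting do not, however, change the endpoint as listed, which still leaves out the end of dosing.

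**On leaving the trial.** Termination is discretionary, the cardiac item speaks only of stopping drug, and an article may leave follow-up after drug discontinuation to the full protocol. The discretion is real, and it is why the loss is possible rather than certain. But the problem is not silence: section 2.8 refers to participation, section 2.9 to withdrawal from the study, and section 2.6 ends adverse-event collection at withdrawal. Those are stated rules.

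**On the figures.** Every loss and response rate in the bias table is assumed. The positive error at equal loss follows directly from giving lost patients in both arms the same response rate. A real imputation model could use the mRS scores scheduled before week 16. The 8-to-28 bounds count all dropout, including consent withdrawals that no rule can recover, and exits after week 16 cannot affect the primary endpoint. All of this stands. The figures show what could happen; they do not estimate what will.

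**Conclusion.** Both points hold and should be fixed. The week-16 limit on the safety endpoint conflicts with dosing to week 24 and with one-year monitoring; the counts follow directly from the protocol. The harm is a truncated arm comparison, not uncollected data, except in patients who are withdrawn.

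The rules on leaving the trial allow an obtainable primary outcome, and all later adverse events, to be lost because of treatment. Whether this biases the result depends on how often investigators use the provision, whether use differs by arm, and how the lost patients would have fared; the protocol informs none of these. Under the assumed scenarios the error ranges from −2.2 to +4.8 points on a planned 20-point difference, and it is zero if lost patients resemble their arm. Confidence is high in the reading of the text; the direction and size of any bias are unknown.

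**What to change.** - **Section 2.10:** define the safety endpoint over the full collection period to week 48, and report week 16 as an additional cut.
- **Sections 2.8 and 2.9:** make the toxicity and medical criteria grounds for stopping study drug. Unless consent is withdrawn, continue the scheduled mRS, including week 16, and adverse-event collection to week 48. Use the observed week-16 mRS in the primary analysis.
- **Leave unchanged:** the stopping thresholds, the sample size and the planned missing-data sensitivity analyses.

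The cost is wording in three sections and a modest visit burden for patients off drug; the visits are already in Table 1. Because patients have been randomized since January 2025 and 58 hospitals take part, this means a protocol amendment. If the consent form changes, section 2.4 requires the consent process to be repeated. Enrolment is planned to December 2026, so an early amendment would protect outcomes not yet observed.

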### Sample size calculation

2.11

The sample size was calculated based on the primary endpoint, defined as the proportion of patients achieving a modified Rankin Scale (mRS) score ≤ 2 at 16 weeks after treatment initiation. Due to the absence of robust published data from randomized controlled trials in this specific patient population, the initial response rate assumptions were derived from limited retrospective studies and clinical experience in patients with severe autoimmune encephalitis.

Under the primary assumption of a 90% response rate in the BCDT followed by daratumumab group and a 70% response rate in the BCDT alone group, with a two-sided significance level of 0.05 (*α* = 0.05) and 80% power (*β* = 0.20), the estimated required sample size was 64 patients per group. After accounting for a 10% dropout rate, approximately 80 participants were estimated for each of the two active comparison groups. For the third group (repeated IVIG/PE), given the anticipated difficulty in recruitment and its role as an exploratory reference arm, the sample size was set at 40 patients. Thus, the total planned sample size was 200 patients.

### Statistical analysis

2.12

#### Definition of the primary efficacy endpoint and event definitions

2.12.1

The primary efficacy endpoint is the proportion of patients with an mRS score ≤ 2, assessed at 16 weeks after treatment initiation.

Relapse event: Defined as the occurrence of new or worsening neurological or psychiatric symptoms attributable to NMDARE following an initial period of at least 2 months of clinical improvement or stabilization, accompanied by at least one of the following: (1) recurrence or an increase in anti-NMDAR antibodies in cerebrospinal fluid (CSF) or serum; (2) new or worsening abnormalities on brain MRI consistent with encephalitis; or (3) new or increased epileptiform activity on EEG. All relapse events must be reviewed and confirmed by an independent adjudication committee (6, 21, 27, 28).

Rescue treatment event: Defined as the initiation of any additional immunotherapy beyond the assigned study treatment due to insufficient clinical improvement, clinical deterioration, or life-threatening complications. This includes, but is not limited to, cyclophosphamide, bortezomib, tocilizumab. The decision to initiate salvage therapy is made by the treating physician and subsequently reviewed and confirmed by the independent adjudication committee (21, 29).

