Plasma cells reside within the central nervous system and its borders, where they contribute to both protective humoral immunity and pathological inflammation (11). Pathological studies found a significant infiltration of antibody-secreting cells (CD38^+^ CD138^+^) into the brain tissue of AE patients (12, 13). These cells are found around blood vessels, within interstitial spaces, and in Virchow-Robin spaces, where they continue to secrete autoantibodies, thus explaining the synthesis of intrathecal antibodies. Traditional B-cell depleting agents, such as rituximab may deplete short-lived plasma cells and plasmablasts derived from activated B cells but not CD20-negative long-lived plasma cells (14), which may contribute to treatment failure in severe NMDARE cases. Given these pathological insights, plasma cell-targeted therapy has emerged as a promising area of research (15). Daratumumab, an anti-CD38 monoclonal antibody, exerts its therapeutic effects by specifically eliminating short-lived and long-lived plasma cells and plasmablasts that express high levels of CD38. The drug has demonstrated high efficacy in multiple myeloma (16) and exhibits immunomodulatory functions on some other cells, including effector memory CD8^+^ T cells (17). Recent case reports indicate that daratumumab has significant potential for the treatment of refractory AE (18, 19). In parallel, the ongoing phase 2B EXTINGUISH trial is evaluating inebilizumab, an anti-CD19 antibody that depletes a broader spectrum of B-lineage cells including plasmablasts and some plasma cells, in a randomized, placebo-controlled design involving 116 patients with moderate-to-severe NMDAR encephalitis, with primary outcome assessed at 16 weeks (20). It remains to be determined whether early use of plasma cell depleting treatment provide more benefits in patients with severe AE. This trial aims to investigate the efficacy of daratumumab add-on ofatumumab in patients with severe AE and autoantibodies against neural surface antigens.

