### Trial design and setting

2.1

RADIA is a randomized, controlled, open-label, multicenter clinical trial initiated by investigators to assess the safety and efficacy of B-cell depleting therapy followed by daratumumab in patients with severe AE, with NMDARE as the primary target population. The study will be conducted in the Department of Neurology in 58 tertiary hospitals nationwide, with a planned enrollment of 200 patients by December 2026.

The study was approved firstly by the Institutional Review Board of the Third Affiliated Hospital of Soochow University. The first patient was randomized in Jan 2025. The participants will be randomly assigned to receive one of three treatment arms: B-cell-depleting agents (ofatumumab followed by daratumumab, B-cell-depleting agents (ofatumumab alone), or repeated IVIG/PE therapy. The flowchart outlining the recruitment, intervention, and evaluation processes is presented in Figure 1.

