#### Inclusion criteria

2.2.1

The patient inclusion criteria were as follows:Aged 12 years and older.Diagnosis of autoimmune encephalitis targeting neural surface antigen, predominantly NMDARE.At least 3 days of high-dose methylprednisolone pulse therapy (500–1000 mg) and IVIG (0.4 g/kg/day for 5 consecutive days), at least 5 sessions of plasma exchange or immunoadsorption, or at least 2 doses of FcRn antagonist efgartigimod have been used.mRS score ≥3 and neuropsychiatric manifestations inadequate to symptomatic treatment.Provision of informed consent by the participant or legal guardian.Negative pregnancy test for women of childbearing potential (up to 2 years postmenopause).

After providing informed consent, participants will enter a 14-day screening period. For individuals unable to provide consent owing to the severity of their condition, a legally authorized representative (or an equivalent individual as specified by local law) may provide informed consent, ensuring compliance with local regulations.

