### Study measurements and data collection

2.6

Disease severity will be evaluated via mRS and CASE, See Table 1 for the specific schedule of assessments for each visit.

**Table 1 tab1:** Schedule of enrolment, interventions, and assessments.

	Study period																			
	Screen	Treatment phase													Follow-up					
Time point (week)	−1	0	1	2	3	4	5	6	7	8	12	16	20	24	28	32	36	40	44	48
Enrolment																				
Informed consent	**×**																			
Demographics	**×**																			
Medical history	**×**																			
Inclusion/exclusion	**×**																			
Intervention																				
Ofatumumab		**×**	**×**	**×**		**×**				**×**	**×**	**×**	**×**	**×**	Depends on the level of memory B cells monitored					
Daratumumab		**×**	**×**	**×**		**×**				**×**	**×**	**×**	**×**	**×**						
Rituximab		**×**												**×**	Depends on the level of memory B cells monitored					
IVIG/PE						**×**				**×**	**×**									
Assessments	×																			
HCG test (for female participants)	**×**																			
Physical examination	**×**	**×**	**×**	**×**	**×**	**×**	**×**	**×**	**×**	**×**	**×**	**×**	**×**	**×**	**×**	**×**	**×**	**×**	**×**	
Clinical blood tests and biochemistry	**×**		**×**	**×**		**×**				**×**	**×**	**×**	**×**	**×**			**×**			**×**
Cerebrospinal fluid (CSF) Analysis	**×**																			
Serum immunoglobulin and anti-NMDAR antibody levels	**×**					**×**				**×**	**×**	**×**	**×**	**×**			**×**			**×**
CSF anti-NMDAR antibody levels)	**×**																			
Lymphocyte Subsets	**×**		**×**	**×**		**×**				**×**	**×**	**×**	**×**	**×**			**×**			**×**
Memory B cells and plasma cell subsets	**×**		**×**	**×**		**×**				**×**	**×**	**×**	**×**	**×**			**×**			**×**
mRS	**×**	**×**	**×**	**×**	**×**	**×**	**×**	**×**	**×**	**×**	**×**	**×**	**×**	**×**	**×**	**×**	**×**	**×**	**×**	**×**
CASE	**×**	**×**	**×**	**×**	**×**	**×**	**×**	**×**	**×**	**×**	**×**	**×**	**×**	**×**	**×**	**×**	**×**	**×**	**×**	**×**
MMSE	**×**	**×**	**×**	**×**	**×**	**×**	**×**	**×**	**×**	**×**	**×**	**×**	**×**	**×**	**×**	**×**	**×**	**×**	**×**	**×**
MOCA	**×**	**×**	**×**	**×**	**×**	**×**	**×**	**×**	**×**	**×**	**×**	**×**	**×**	**×**	**×**	**×**	**×**	**×**	**×**	**×**
NPI	**×**	**×**	**×**	**×**	**×**	**×**	**×**	**×**	**×**	**×**	**×**	**×**	**×**	**×**	**×**	**×**	**×**	**×**	**×**	**×**
Imaging	**×**													**×**						**×**

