#### Analysis methods for primary and secondary endpoints

2.12.2

For the primary endpoint, the comparison of the proportion of patients achieving mRS ≤ 2 at week 16 between treatment groups will be performed using a Cochran–Mantel–Haenszel test stratified by study center, with a two-sided significance level of 0.05. A logistic regression model adjusting for stratification factors and baseline covariates (e.g., age, baseline mRS) will be used as a supportive analysis.

For time-to-event endpoints, including relapse and salvage treatment events, Kaplan–Meier curves will be used to summarize event times, and event rates with 25%/75% quartiles will be calculated. The stratified log-rank test will be used for intergroup comparisons, and hazard ratios with 95% confidence intervals will be estimated using a Cox proportional hazards model, with stratification factors included as covariates.

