#### Analysis populations

2.12.4

The Intent-to-Treat (ITT) population was defined as all randomized patients who received at least one dose of the study drug. The Full Analysis Set (FAS) population was defined as patients who met the inclusion criteria and completed at least one efficacy assessment. The primary analysis will be performed on the ITT population. If the difference in key baseline characteristics or primary outcome between the FAS and ITT populations exceeds 5%, the primary analysis will additionally be performed on the FAS population.

For patients who withdraw from the study due to severe adverse events or other reasons, data after withdrawal will be handled using last observation carried forward (LOCF) in sensitivity analyses. For time-to-event analyses, such patients will be censored at the time of withdrawal under the non-informative censoring assumption.

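### Relapse is defined for NMDARE only, but the trial also enrols other surface-antigen encephalitis and states no restriction of the relapse analysis, so the relapse rate would be understated

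*Protocol article*

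**What the plan says.** **Who is enrolled.** Inclusion criteria (section 2.2.1): "Diagnosis of autoimmune encephalitis targeting neural surface antigen, predominantly NMDARE". The Introduction states the aim for "patients with severe AE and autoantibodies against neural surface antigens" and names LGI1, GABABR and CASPR2 encephalitis as other types. Section 2.1 describes the trial "with NMDARE as the primary target population", which makes NMDARE the main population but not the only one.

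**What counts as a relapse.** Section 2.12.1 requires "new or worsening neurological or psychiatric symptoms attributable to NMDARE following an initial period of at least 2 months of clinical improvement or stabilization", together with at least one of three supporting findings. The first is "recurrence or an increase in anti-NMDAR antibodies in cerebrospinal fluid (CSF) or serum"; the other two are MRI changes and EEG changes, neither tied to a subtype. An independent committee must confirm every relapse.

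**How relapse is analysed.** Section 2.12.2: "For time-to-event endpoints, including relapse and salvage treatment events, Kaplan–Meier curves will be used to summarize event times", followed by a stratified log-rank test and a Cox model. Section 2.12.4 defines the ITT set as "all randomized patients who received at least one dose of the study drug". It also defines an FAS that is not limited by subtype, and it gives a censoring rule for withdrawal only. Randomisation (section 2.3) is stratified by centre alone.

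**Which antibody is measured.** The serial serum row of Table 1 reads "Serum immunoglobulin and anti-NMDAR antibody levels", and the CSF antibody row likewise names anti-NMDAR. The text of section 2.6 instead plans titres of anti-neuronal antibodies at baseline and week 16, and section 2.10 lists change in serum autoantibody as a secondary endpoint. Both are worded for any antibody.

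**The concern.** The event definition is narrower than the eligible population. A patient with, say, LGI1 encephalitis could have a clear clinical relapse with new MRI and EEG findings and still not meet the definition, because the symptoms are not attributable to NMDARE. If that patient is followed in the relapse analysis, the time counts as event-free. The reported relapse rate for the enrolled population would then be too low, and a comparison that is probably already short of events would lose more.

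This is not a detail left to a later document. The article fixes a definition, and that definition does not fit its own inclusion criteria. An analysis plan that copied it would inherit the mismatch.

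**Working it through.** **Step 1. Is there a route by which a non-NMDARE relapse counts?**

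| Element | Where | Open to other subtypes? |
|---|---|---|
| Attribution of symptoms (mandatory) | 2.12.1 | No, NMDARE only |
| Antibody criterion | 2.12.1 | No, anti-NMDAR only |
| MRI or EEG criterion | 2.12.1 | Yes, but only in addition to the attribution |
| Parallel definition for other subtypes | – | None shown |
| Restriction of the relapse analysis to NMDARE | 2.12.2, 2.12.4 | None shown |

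On the literal text there is no such route.

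**Step 2. Figures in the plan.** The article gives no relapse rate, event count or power for relapse, so there is no figure to reproduce. Its sample size (64 per group before dropout, for 90% versus 70%) rests on week-16 mRS. A pooled-variance calculation gives 62, close to the stated 64, and the relapse definition does not enter it.

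**Step 3. Effect on the relapse rate.** Let q be the non-NMDARE share, not stated and assumed here to be 10–30% (20 to 60 of 200 patients). With similar relapse risk across subtypes:

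- counted events = (1 − q) × all events
- apparent Kaplan–Meier risk = (1 − q) × true risk

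So 10–30% of relapses are lost.

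**Step 4. Illustration.** Further assumptions, none from the article: 48-week relapse risk of 20% on ofatumumab alone, true hazard ratio 0.5, 80 patients per arm.

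- Risk in the combination arm: 1 − 0.80^0.5 = 10.6%.
- Expected events if all subtypes count: 80 × (0.200 + 0.1056) = 24.4.
- Power by Schoenfeld's formula: Φ(√(events/4) × ln 2 − 1.96).
- Apparent hazard ratio, as a ratio of cumulative hazards: ln(1 − 0.1056(1 − q)) / ln(1 − 0.20(1 − q)).

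| q | Apparent risks | Events counted | Power | Apparent hazard ratio |
|---|---|---|---|---|
| 0% | 20.0% vs 10.6% | 24.4 | 40% | 0.500 |
| 10% | 18.0% vs 9.5% | 22.0 | 37% | 0.503 |
| 20% | 16.0% vs 8.4% | 19.6 | 34% | 0.506 |
| 30% | 14.0% vs 7.4% | 17.1 | 30% | 0.509 |

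With q equal in both arms, absolute risks and event counts fall but the hazard ratio hardly moves.

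**Step 5. Chance imbalance in subtype.** At q = 20%, the SD of the between-arm difference in q is:

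- two arms of 80: √(2 × 0.2 × 0.8 / 80) = 0.063
- 80 versus 40: √(0.16 × (1/80 + 1/40)) = 0.077

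For the two larger arms, a one-SD imbalance shifts the log hazard ratio by about 0.063/0.8 = 0.08. The standard error of the log hazard ratio with 19.6 events is about 2/√19.6 = 0.45. Imbalance therefore adds about (0.08/0.45)² ≈ 3% to the variance.

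**The case against.** **It looks like a drafting slip.** Section 2.4 also uses NMDARE as shorthand: its rule for participants who cannot consent mentions only NMDARE-related symptoms, although it must serve all enrolled patients. The committee might read the relapse definition in the same spirit. This softens the point, and it means one should not say the committee is bound to reject true relapses. But the text gives it no basis for the wider reading, and different members could read it differently.

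**The risk set is inferred from silence.** Section 2.12.4 assigns the ITT set to the primary analysis and names no set for time-to-event endpoints; an unseen analysis plan could restrict relapse to NMDARE. This stands as a limit. Such a restriction would settle the matter, and it is one of the two remedies below.

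**Relapse has a minor role.** It is absent from the endpoint list in section 2.10 and from the abstract's outcomes. In the illustration, power is only about 40% even with every relapse counted. This stands and keeps the point modest, although section 2.12.2 does prescribe a formal comparison.

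**Stronger readings the documents do not support.**

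- A reader might infer from Table 1 that non-NMDARE patients never have their own antibody measured. Sections 2.6 and 2.10 plan generic antibody testing at baseline and week 16. What remains is a mismatch: the serial serum schedule (screening, then weeks 4 to 48) is labelled for anti-NMDAR only, and that schedule is the one more likely to show a rise at relapse.
- A reader might infer that the hazard ratio is biased. With balanced subtypes it barely changes, and chance imbalance under randomisation is small random error rather than systematic bias.
- A reader might infer that the primary analysis should be stratified by subtype. That does not follow from a mismatch in the relapse definition.

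**Conclusion.** The point holds as an inconsistency between eligibility and event definition. Applied as written, and with no restriction of the analysis, the rule leaves relapses outside NMDARE uncounted and understates the whole-population relapse rate by roughly the non-NMDARE share. At an assumed share of 10–30% with similar relapse risk across subtypes, that is 10–30% of relapses. If NMDARE predominates more strongly than this, the loss is smaller.

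The consequence is a low absolute relapse rate and fewer events, not a distorted treatment effect. The primary mRS endpoint and the sample size are unaffected. The Table 1 antibody labels are a related, smaller inconsistency with sections 2.6 and 2.10. The point is worth correcting because correction is cheap, but it does not threaten the trial's main conclusion.

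**What to change.** Choose one of two wordings for section 2.12.1 and carry it through.

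1. **Preferred.** Define relapse as new or worsening symptoms attributable to the patient's index autoimmune encephalitis, with the antibody criterion read as recurrence or rise of the index neural-surface antibody. Keep the MRI and EEG criteria as they are. Relabel the Table 1 antibody rows to the index antibody, so that they agree with sections 2.6 and 2.10.
2. **Alternative.** Keep the NMDARE definition and state in section 2.12.2 that relapse is analysed in NMDARE patients only. Table 1 still needs aligning with the generic antibody endpoint. The price is that relapse in other subtypes goes unreported.

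The cost is a few lines of text and, under the first option, a small number of matched serial assays for non-NMDARE patients at the central laboratory, which already runs cell-based assays. Enrolment is planned to December 2026, so the wording can be settled before analysis. Any suspected relapse already adjudicated in a non-NMDARE patient should be re-reviewed under the revised definition.
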